# Progressive Transition From Supervised to Unsupervised Robot-Assisted Therapy After Stroke: Protocol for a Single-Group, Interventional Feasibility Study

**DOI:** 10.2196/48485

**Published:** 2023-11-09

**Keywords:** technology-assisted rehabilitation, unsupervised therapy, self-directed therapy, stroke, neurorehabilitation, neurocognitive rehabilitation, robot-assisted therapy, rehabilitation technology, robot.

## Abstract

**Background:**

Increasing the dose of therapy delivered to patients with stroke may improve functional outcomes and quality of life. Unsupervised technology-assisted rehabilitation is a promising way to increase the dose of therapy without dramatically increasing the burden on the health care system. Despite the many existing technologies for unsupervised rehabilitation, active rehabilitation robots have rarely been tested in a fully unsupervised way. Furthermore, the outcomes of unsupervised technology-assisted therapy (eg, feasibility, acceptance, and increase in therapy dose) vary widely. This might be due to the use of different technologies as well as to the broad range of methods applied to teach the patients how to independently train with a technology.

**Objective:**

This paper describes the study design of a clinical study investigating the feasibility of unsupervised therapy with an active robot and of a systematic approach for the progressive transition from supervised to unsupervised use of a rehabilitation technology in a clinical setting. The effect of unsupervised therapy on achievable therapy dose, user experience in this therapy setting, and the usability of the rehabilitation technology are also evaluated.

**Methods:**

Participants of the clinical study are inpatients of a rehabilitation clinic with subacute stroke undergoing a 4-week intervention where they train with a hand rehabilitation robot. The first week of the intervention is supervised by a therapist, who teaches participants how to interact and train with the device. The second week consists of minimally supervised therapy, where the therapist is present but intervenes only if needed as participants exercise with the device. If the participants properly learn how to train with the device, they proceed to the unsupervised phase and train without any supervision during the third and fourth weeks. Throughout the duration of the study, data on feasibility and therapy dose (ie, duration and repetitions) are collected. Usability and user experience are evaluated at the end of the second (ie, minimally supervised) and fourth (ie, unsupervised) weeks, allowing us to investigate the effect of therapist absence.

**Results:**

As of April 2023, 13 patients were recruited and completed the protocol, with no reported adverse events.

**Conclusions:**

This study will inform on the feasibility of fully unsupervised rehabilitation with an active rehabilitation robot in a clinical setting and its effect on therapy dose. Furthermore, if successful, the proposed systematic approach for a progressive transition from supervised to unsupervised technology-assisted rehabilitation could serve as a benchmark to allow for easier comparisons between different technologies. This approach could also be extended to the application of such technologies in the home environment, as the supervised and minimally supervised sessions could be performed in the clinic, followed by unsupervised therapy at home after discharge.

**Trial Registration:**

ClinicalTrials.gov NCT04388891; https://clinicaltrials.gov/study/NCT04388891

**International Registered Report Identifier (IRRID):**

DERR1-10.2196/48485

## Introduction

Stroke survivors often do not entirely recover upper limb function [1], which severely impacts independence and quality of life as remaining upper limb impairments may limit their ability to perform activities of daily living. Increasing evidence shows that therapy dose is a key factor contributing to sensorimotor recovery and that administering a higher dose of upper limb therapy to people after stroke could improve their functional outcome even long after stroke [2,3].

However, due to factors such as unfavorable therapist to patient ratios [4], high rehabilitation-related costs, and the overall frailty of health care systems (as highlighted, for example, by the COVID-19 pandemic [5,6]), increasing the dose of high-quality therapy for both inpatients and outpatients is challenging as long as it relies on hospital visits and supervised therapy.

Unsupervised technology-assisted rehabilitation, defined here as patients training with rehabilitation technologies without any supervision by an external person, is a promising solution to increase therapy dose without dramatically weighing on the health care system [7]. Relying on novel digital approaches, such as wearable sensors or robotic tools, offers new ways to promote motivation and engagement for specific therapy exercises. It promises to go beyond the conventional set of exercises prescribed for patients to train independently, which may lead to low adherence [8,9]. A range of upper limb rehabilitation technologies have been tested in unsupervised settings, such as the home environment, with varying results regarding acceptance, satisfaction, success, and amount of use [10-15]. Besides the use of different technologies, these outcomes may also be influenced by the different methods applied to teach the patients how to use a rehabilitation technology in an independent way. A key step for the successful and safe use of a rehabilitation technology without supervision is the progressive transition toward unsupervised use, where users first learn how to correctly use a technology. This becomes especially critical in the case of active technologies, such as rehabilitation robotics, whose use without any external supervision has rarely been reported.

Unfortunately, most existing studies only report little information on these methodological steps or use very different protocols (eg, from multiple training sessions in supervised settings [11] to a single explanation session directly at home [12]). Similarly, there is a lack of agreement on objective measures to evaluate and document the feasibility and success of unsupervised training.

In this protocol paper, we report on the study design of a single-group, interventional clinical study to test the feasibility of fully unsupervised therapy with an active hand rehabilitation robot in patients with subacute stroke. More specifically, we describe in detail a study protocol with the following aims: (1) to evaluate the feasibility of unsupervised therapy assisted by an active rehabilitation robot and a standardized approach for the progressive transition from supervised to unsupervised use based on a set of well-defined and objective criteria, (2) to investigate the effect of unsupervised therapy on achievable therapy dose during rehabilitation, and (3) to evaluate user experience as well as the usability of the rehabilitation technology.

The secondary objective of this study is to identify patient-related parameters (eg, age, cognitive abilities, level of impairment) that might influence the ability of a user to transition to unsupervised therapy and the dose of self-administered therapy.

## Methods

### Study Population and Recruitment

For this study, we aim to recruit patients in the subacute phase after stroke that are currently undergoing rehabilitation (inpatients). To be eligible for the study, patients must fulfill all the following inclusion criteria: (1) be between 18 and 90 years old, (2) be within 6 weeks from stroke onset, (3) have a prestroke Modified Rankin Score [16] ≤1, (4) have a National Institutes of Health Stroke Scale [17] score ≥1 in at least one of the items concerning motor or sensory function and ataxia, and (5) have provided informed consent as documented by a signature.

Patients are excluded if one of the following exclusion criteria is present: (1) moderate to severe aphasia (Goodglass-Kaplan scale [18] <3), (2) moderate to severe cognitive deficits (levels of cognitive functioning-revised [19] <8), (3) functional impairment of the upper limb due to other pathologies, (4) severe pain in the affected arm (visual analogue scale [VAS] for pain ≥5), (5) other pathologies that may interfere with the study, (6) pacemakers and other active implants, and (7) a modified Ashworth Scale [20] >2 for one or more of the following muscles: shoulder adductors, forearm pronator and supinator, and flexors and extensors of the elbow, wrist, and fingers.

The study is recruiting inpatients with stroke from the Clinica Hildebrand Centro di Riabilitazione Brissago, a rehabilitation clinic in Switzerland where the rehabilitation technology used in the study is available. One of the medical doctors of the rehabilitation clinic involved in the study proposes to patients potentially meeting the eligibility criteria to participate in the study, explains the protocol, and obtains informed consent from them. Compensation is not provided.

### The ReHapticKnob

The rehabilitation technology used in this study is the ReHapticKnob (RHK; Figure 1), which consists of a haptic device for the rehabilitation of hand sensorimotor function after stroke with 2 active degrees of freedom, allowing for hand opening and closing and forearm pronosupination [21].

**Figure 1 figure1:**
[figure not shown]
A patient with stroke performing an exercise with the ReHapticKnob. During a therapy session with the device (left), users first log in to their personal therapy account with a fingerprint reader; then, when performing the exercises, they place their fingers on the handles and interact with the virtual reality interface by using a colored pushbutton keyboard. As the exercises implemented on the ReHapticKnob require the user to solve tasks by relying on the sensorimotor information coming from the impaired limb and not on visual information, view of the impaired hand is blocked with a hand cover. The ReHapticKnob allows for grasping (top right) and forearm pronosupination (bottom right) movements.

The rehabilitation exercises implemented on the RHK follow the neurocognitive therapy approach [22-24] and promote motor learning by focusing on sensorimotor integration, as they require patients to use kinesthetic and proprioceptive information from their impaired upper limb and cognitively process it to solve the therapy tasks in the correct way. Assessment-driven exercises ensure an optimal difficulty level from the beginning while ensuring dynamic difficulty adaptation based on the user’s performance [25]. Therapy with the RHK was previously shown to be as efficient as dose-matched conventional therapy [26] when performed in supervised settings.

To make the device suitable for unsupervised use, design changes, such as the implementation of a new graphical user interface and pushbutton keyboard to allow direct interaction between the user and the device, were implemented and tested in a previous usability study [24]. Building on that work, the usability of the platform was further improved by implementing minor graphical changes and audio instructions for the exercises. Furthermore, the platform was improved by integrating clinically inspired algorithms to automatically monitor, control, and adapt therapy in a personalized way [27,28]. This set of algorithms was evaluated in a pilot study with 5 patients with subacute stroke, demonstrating its ability to guide them through several therapy sessions with the RHK and to automatically adapt the difficulty level of the exercises to keep therapy challenging.

### Intervention

This trial is a single-group, interventional clinical study. The study protocol lasts for about 4 weeks for each patient (Figure 2), which is compatible with the duration of an inpatient stay at the rehabilitation clinic and comparable to our previous studies with the RHK [26]. The data collected and procedures performed at each time point are listed in Table 1.

**Figure 2 figure2:**
[figure not shown]
Design of the interventional study for each of the study participants. All participants undergo a screening visit, baseline assessments, 1 week of supervised therapy, and 1 week of minimally supervised therapy. After the first week of minimally supervised therapy, the therapist checks whether the patient properly learned how to use the technology and is ready for unsupervised training. If yes, the patient proceeds to 2 weeks of unsupervised use. If no, an additional week of minimally supervised therapy is performed. At the end of this second week, the therapist checks again whether the patient can train independently. If yes, the patient proceeds to 1 week of unsupervised therapy. If no, an additional week of minimally supervised therapy is performed. In total, each patient performs 4 weeks of technology-assisted rehabilitation. At the end of the protocol, the clinical and robotic assessments as well as the evaluation of the user experience and usability are repeated for all patients.

**Table 1 table1:** Data collected and procedures (marked with an “X”) performed at each time point of the clinical trial, with primary (PO) and secondary (SO) outcomes indicated. Day 0 corresponds to the first supervised robot-assisted therapy session. The time range indicates how far a procedure can be advanced (–) or postponed (+) for organizational reasons from the precise time point at which it should be performed.

		Screening visit	Baseline clinical assessment	Baseline robotic assessment	Robot-assisted therapy sessions		Usability evaluation 1	Robot-assisted therapy sessions		Final clinical assessment	Final robotic assessment	Usability evaluation 2
Time point		Day –2	Day –1	Day –1	Day 0-6	Day 7-13	Day 13	Day 14-20	Day 21-27	Day 27	Day 27	Day 27
Time range (days)		–4 to +1	±2	±1	—^a^	—	±2	—	—	±2	±2	±2

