Before starting the intervention, patients undergo a screening visit with a medical doctor at which the eligibility criteria are checked and demographic and medical data relevant for patient characterization are collected. At the beginning and end of the study, patients undergo a visit with an experienced therapist where clinical assessments are performed to characterize upper limb sensorimotor deficits. Before the first robot-assisted therapy session and at the end of the study, robotic assessments are performed. The baseline robotic assessments are used to tailor the initial difficulty level of the therapy exercises. As robotic therapy is an addition to conventional therapy and this protocol does not comprise a control group, functional recovery is not used to evaluate the efficacy of unsupervised robot-assisted therapy, as it is not possible to infer how much of the recovery is due solely to the addition of robotic therapy, but rather to investigate the possible relation of different impairment profiles on the observed increase in therapy dose.

During the first week of intervention (ie, the supervised phase), a therapist familiarizes the participants with the therapy platform and teaches them how to perform the therapy exercises. During the second week (ie, the minimally supervised phase), participants try to perform the therapy exercises with the device by themselves. A therapist is still present in the room but intervenes only upon request or if deemed to be needed. The first 2 phases consist of 5 sessions of about 45 minutes each, performed on consecutive days (weekends excluded). These sessions are an addition to standard therapy. Therefore, during the study, participants are allowed to fully follow the conventional interdisciplinary rehabilitation program provided by the clinic.

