The usability of the platform and user experience during robot-assisted therapy is rated a first time at the end of the first week of minimally supervised therapy and a second time at the end of the study. The difference in the ratings between the 2 time points is used to investigate the effect of unsupervised training (ie, of the therapist’s absence) on the perceived usability of the therapy platform and on the user experience during technology-assisted rehabilitation.

Adverse events and device deficiencies are monitored throughout the whole study protocol. The intervention can be discontinued after consultation with medical doctors and therapists or if the participant decides to quit.

For each patient, attendance to the robot-assisted therapy sessions is registered. As attendance to robot-assisted therapy is one of the study outcomes, strategies to increase adherence are not implemented. Reasons for nonattendance are registered a posteriori for each missed supervised or minimally supervised session as well as if patients train for less than 50% of the possible days (ie, less than 7 of 14 days when the patient undergoes 2 weeks of unsupervised therapy or less than 4 of 7 days in cases where the patient undergoes only 1 week of independent training) during the unsupervised phase.

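### Table 1's windows let the therapist-present usability rating fall up to two days into open unsupervised access, and let the clinical baseline fall after the first session

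*Protocol article*

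**What the plan says.** All places are in the protocol article, Methods.

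- **Table 1, legend and header rows.** The time origin is fixed: "Day 0 corresponds to the first supervised robot-assisted therapy session". The time range is defined as "how far a procedure can be advanced (–) or postponed (+) for organizational reasons from the precise time point". Screening is at day -2 (-4 to +1), the clinical baseline at day -1 (±2), the robotic baseline at day -1 (±1), usability evaluation 1 at day 13 (±2) and usability evaluation 2 at day 27 (±2). Unsupervised therapy occupies days 14-20 and 21-27.
- **Intervention, on the first rating.** The platform "is rated a first time at the end of the first week of minimally supervised therapy". The change to the second rating "is used to investigate the effect of unsupervised training (ie, of the therapist’s absence) on the perceived usability".
- **Figure 2 caption.** The order is screening, baseline assessments, supervised week, minimally supervised week, checklist, and then unsupervised therapy for those who pass. Those who do not pass stay minimally supervised for another week.
- **Primary Outcomes and Data Analysis.** The difference in usability and user experience between therapist-present phases and the unsupervised phase is listed as primary, although Table 1 marks the same questionnaires as secondary (SO). It is tested with a paired t test or Wilcoxon test of evaluation 1 against evaluation 2.
- **Secondary Outcomes and Data Analysis.** Baseline clinical scores enter functional recovery and the models for factors influencing dose.

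**The concern.** The evaluation 1 to evaluation 2 contrast can be attributed to the therapist's absence only if the first rating reflects use with a therapist in the room. A patient who passes the checklist and rates the platform on day 14 or 15 may already have trained alone. If the therapist's absence shifts ratings, part of that shift may then sit in the reference rating, and the difference shrinks. The Discussion expects no drop in usability or user experience during unsupervised use, so dilution would favour the expected result.

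The clinical baseline raises the same kind of question on a smaller scale: a score taken after therapy has begun is not strictly a baseline for functional recovery or for the analysis of dose predictors.

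**Working it through.** **Check of the calendar.** Table 1 has unsupervised therapy from day 14 to day 27, which is 27 - 14 + 1 = 14 days, or from day 21 for a late transition, which is 27 - 21 + 1 = 7 days. Both agree with the Intervention section's threshold for recording reasons for low attendance ("less than 7 of 14 days when the patient undergoes 2 weeks of unsupervised therapy", and 7 days for the one-week case). Day 14 is therefore the first unsupervised day for a patient who passes the first checklist.

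**Windows (nominal day plus stated offsets).**

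| Procedure | Calculation | Permitted days | Boundary | Days on or past it |
|---|---|---|---|---|
| Usability evaluation 1 | 13 - 2 to 13 + 2 | 11 to 15 | unsupervised start, day 14 | 14, 15 (2 of 5) |
| Clinical baseline | -1 - 2 to -1 + 2 | -3 to +1 | first session, day 0 | 0, +1 (2 of 5) |
| Robotic baseline | -1 - 1 to -1 + 1 | -2 to 0 | first session, day 0 | 0 |

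For the clinical baseline, day +1 always follows the first session, while day 0 may fall before or after it. The robotic baseline on day 0 raises no problem, because the Intervention section expressly places it before the first session. The clinical baseline has no such sentence; there the order comes only from the Figure 2 caption.

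**Exposure before evaluation 1.** At the latest permitted date, 15 - 14 + 1 = 2 of the 14 unsupervised days have opened. This applies only to patients who pass the first checklist. For the others a therapist is still present on days 14 and 15.

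**Is the late margin likely to be needed?** Sessions skip weekends. If day 0 is a Monday (an assumption), the ten sessions end on Friday, day 11, and day 13 is a Sunday. The rating then has to move unless staff work on Sunday: back to day 11 or forward to day 14. If day 0 is any other weekday, the tenth session is on day 13 itself. In every case the tenth session lies within days 11 to 13, so the plus side is not needed to reach it.

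**Size of a possible dilution.** The documents give no visit dates, so only a bound per late rating is possible. Let *D* be the mean change due to the therapist's absence, *n* the number of pairs, *k* the number rated late, and *s* (0 to 1) the share of the change already present in a late rating. With equal effects across patients (an assumption),

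expected observed change = *D* × (1 - *k* × *s* / *n*).

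For one late rating with *s* = 1, the loss is 1/13 = 7.7% of *D* with 13 pairs, or 1/10 = 10% with the 10 patients that the Sample Size section regards as sufficient. With *s* = 0 there is no loss. *k* and *s* are unknown.

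**After closing the plus side.** Evaluation 1 at -2 to 0 gives days 11 to 13, with no day in the unsupervised phase. The clinical baseline at -2 to 0 gives days -3 to -1, with no day on or after day 0.

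**The case against.** The strongest reply is that Table 1 only gives tolerances, while the order of procedures is set by the Figure 2 caption and the Intervention text. Some tolerance around day 13 is unavoidable because of weekends. Patients may choose not to train at all in the unsupervised phase, so days 14 and 15 are days of access, not necessarily of use. At most 2 of 14 days are affected, and only for those who pass the first checklist. For the clinical baseline, exposure by day +1 is one or two sessions of about 45 minutes, and the Intervention section says that functional recovery does not serve to judge efficacy.

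Most of this stands and limits the weight of the point. It does not remove it. Nothing in the table or its footnotes makes the windows subject to the order of procedures. The table can also express a one-sided limit when wanted: the screening range of -4 to +1 stops at day -2 + 1 = -1, before therapy. The weekend argument justifies the minus side of the day-13 window, not the plus side.

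A reader might also infer that the plan allows assessments before consent. By offsets alone, screening covers days -6 to -1, and 3 of the 6 × 5 = 30 day combinations put the clinical baseline first. The documents do not support that reading. Signed consent is an inclusion criterion, the Figure 2 caption puts screening before baseline, the text states "Before starting the intervention, patients undergo a screening visit with a medical doctor at which the eligibility criteria are checked", and the Ethical Considerations commit the study to good clinical practice.

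**Conclusion.** The point holds in a narrow form. Table 1's window for usability evaluation 1 contradicts the Intervention text on 2 of its 5 permitted days, for patients who transition at the first checklist. The consequence is a possible dilution of the contrast, not its loss: up to 2 of 14 optional unsupervised days before the rating, and at most 7.7% to 10% of the mean change per late rating under the assumptions shown. The direction also rests on an assumption, namely that early unsupervised use moves ratings the same way as the full phase and by no more. It matters because this contrast is the planned evidence on the therapist's absence and is called primary in the text, though its SO label in Table 1 leaves its rank unclear.

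The clinical baseline overlap is a secondary inconsistency with a probably small effect on functional recovery and the predictor analyses.

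It would go too far to infer that any rating or baseline was actually late. The documents give no visit dates.

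**What to change.** **Wording.** State that usability evaluation 1 takes place after the last session of the first minimally supervised week and before the first unsupervised login, for example day 13 with -2 to 0. The event rule should govern, because for some start days the early part of that range precedes the tenth session. State that the clinical baseline takes place after screening and before the first session.

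**Data handling.** All 13 patients have completed, so new wording cannot change conduct; the useful step now is a date check.

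1. Compare each evaluation 1 date with the patient's first unsupervised login. Login times are among the robotic therapy data in Table 1; the evaluation dates are presumably on the case report form.
2. Report how many ratings were late.
3. Run the paired usability contrast with and without them, naming the main analysis before looking at the results. Either choice is defensible.
4. Flag any clinical baseline taken after session 1.

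**Cost.** Two table cells, a sentence or two, and a date comparison. If any rating was late, one of the two analyses has fewer pairs; how many cannot be told from the documents. The corrected windows also matter for later users, since the Discussion offers this approach as a benchmark.
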